### Surgical intervention

The patients for the study will be randomly divided in two groups. Group A: Gamma3 nail (Stryker) and Group B: InterTan (IT) nail (Smith & Nephew). The surgery will take place in one specific operating room with the standardized surgical technique, using the same c-arm for the intra-operative radiological evaluation. Anatomical reduction of the fracture will be intended in all cases prior to nail insertion. If this is not possible, several techniques of closed or open reduction will be applied in order to achieve an acceptable fixation of the fracture. The patients’ position will be on the traction table, using a minimal approach. The lag screw(s) in both groups will be put in the center of the femoral head in the lateral and anteroposterior X-ray view, while the Tip to Apex Distance (TAD) will be approximately 20 mm. All participants in both groups will receive the same physical therapy and adequate anti-osteoporotic treatment.

#### Radiographic evaluation

A standard technique will be kept, in order to have the same parameters in all radiographs. For the antero-posterior ones of the pelvis, both legs of the patients will be rotated inwards 15°. The radiographic measurements will be monitored by two distinguished examiners through RadiAnt DICOM Viewer. Intra-class correlation coefficients (ICC) will check the inter- and intra-rater reliability. The parameters that will be radiographically evaluated are the TAD, the position of the chephalomedulary nail in the femur head and the alignment [42]. Moreover, throughout the follow-up the varus malalignment of the implant will be assessed, as well as the cut-out of the nail and the percentage of nonunion or malunion. Varus collapse is a rotation of the proximal part of the femur anteriorly for at least 3°.

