**Discussion:**

This study will be the first to compare clinical, radiological and biomechanical measurements of the two different cephalomedullary nails. Our main hypothesis is that the IT nail would provide better radiological outcome and probably better clinical results than the Gama3 nail.

*Clinical trial registration* International Standard Randomized Controlled Trial Number (ISRCTN): https://doi.org/10.1186/ISRCTN15588442, registered on 19/4/2022.

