## Materials and methods

### Biomechanical study

#### Implants

The experimental work will be undertaken in the Laboratory of Technology and Strength of Materials at the Department of Mechanical Engineering and Aeronautics of Patras University. Two implant systems will be compared against biomechanical testing, the classic Gamma3 and the InterTan nail (IT).

The Gamma3®nail (Stryker, Mahwah, NJ, USA) that would be used in the current study has a length of 180 mm, 11 mm nail diameter and 130° neck-shaft angle and utilizes a single lag screw with a standard diameter of 10.5 mm. The Trigen Intertan (Smith + Nephew, Watford, UK) nail is a current generation IM device, featuring a dual lag screw configuration comprised of a 11.0 mm superior lag screw and a 7.0 mm smaller integrated screw that allows for linear compression of the fragments at the fracture site while providing high rotational stability [32, 33]. The proximal part of the nail has a trapezoid design that provides a pressfit fixation in the metaphyseal region thus positioning more material on the lateral side of the nail where tensile/stretching forces tend to be greatest. Finally, the “clothes pin” distal tip provides less rigidity to decrease the stress riser and reduce the incidence of anterior thigh pain. An 11 mm nail with a 130° neck-shaft angle will be used for the present study.

We would hypothesize that the above variations, may create differences in strain distribution and thus dissimilar biomechanical behaviors of these two nails. The main hypothesis of our biomechanical study is that the InterTan nail would provide higher stiffness and load to failure and less varus collapse in unstable intertrochanteric fractures (AO/OTA A2). The transmission of forces as measured by cortical surface-strain distribution in the proximal femur will be evaluated using digital image correlation (DIC) and classic strain gauges.

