#### Primary objective

The *primary aim* of this study is to investigate if there are any significant differences in the main radiological measurements (cut-out, varus displacement, loss of reduction, malunion, nonunion) between Gamma3 and IT in closed unstable intertrochanteric fractures (31A2_1–3_) in patients aged over 70 years old at the 24-week follow-up evaluation.

The *second primary aim* would be the functional status at the 24-week follow-up using patient reported disease-specific scores (Harris Hip score HHS-and Oxford hip score-OHS).

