#### Concealment mechanism

For each surgical session patient details and the randomized treatment will be sealed in an opaque envelope that will be given to the coordinated nurse just before the start of the intervention. The patients, relatives, investigators, nurses, and all relevant personnel would be blinded to the indented treatment. The envelope will be opened by the coordinated nurse after the patient is sedated and placed to the radiological table, the hip is properly prepared and the surgeons are ready to apply the intervention. Both instrumentations for Gamma3 or IT would be available at the operative room. After opening the envelope, the procedure will be unblinded for all participants.

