### Limitations

Our study has several limitations. Firstly, the surgery will be performed by several orthopedic surgeons of our department that have different surgical experience, but they all were trained at the same hospital and the reduction will be closed monitored to be as anatomical as possible. Second, the assessment of fracture healing, cut-out, varus displacement and other complications will be measured with digitalized radiographs that can be misinterpreted by wrong patient positioning and intraobserver variability. Third, there are many factors contributing to fracture healing and regain of functional status that are mostly patient depended, especially in these fragile population of > 70 years old. The main weaknesses of the biomechanical study are its static nature and uniplanar loading configuration. Mechanical failure is a dynamic event in clinical practice, and rotational displacement is equally important to frontal plane displacement postoperatively. However, the current study will test the initial loading characteristics of various lag screw(s) configurations at subcritical stress levels and can serve both as a guide at events at early postoperative ambulation status and as a reference for future dynamic studies with more complex loading characteristics.

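### No reader masking is stated for the film-read primary outcome, and the nail shows on every film, so the reads are open to a lean towards InterTan

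*Protocol article*

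**What the plan says.** Under Primary objective, the first primary aim is a difference between the nails in the "main radiological measurements (cut-out, varus displacement, loss of reduction, malunion, nonunion") at 24 weeks. The clinical Statistical analysis section treats radiological device failure as a yes/no outcome and analyses it by logistic regression on nail type.

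Under Radiographic evaluation, "The radiographic measurements will be monitored by two distinguished examiners through RadiAnt DICOM Viewer". Leg rotation is standardised, and inter- and intra-rater ICCs are planned. The same section gives an angular threshold: "Varus collapse is a rotation of the proximal part of the femur anteriorly for at least 3" degrees. It says nothing about masking the examiners, the order in which films are read, or whether the examiners are independent of the operating surgeons.

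Under Implants, the Gamma3 "utilizes a single lag screw with a standard diameter of 10.5 mm", while the InterTan is described as "featuring a dual lag screw configuration comprised of a 11.0 mm superior lag screw and a 7.0 mm smaller integrated screw".

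Under Concealment mechanism, blinding lasts until the patient is ready for the procedure: "After opening the envelope, the procedure will be unblinded for all participants". No later masking of outcome assessment is described.

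The Discussion paragraph of the Abstract gives the expected direction: "Our main hypothesis is that the IT nail would provide better radiological outcome". Under Limitations, the reading risk is put down to "digitalized radiographs that can be misinterpreted by wrong patient positioning and intraobserver variability". Knowledge of the nail is not mentioned.

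**The concern.** Anyone reading an unmodified hip film can tell which nail is in place. Varus displacement and loss of reduction are naturally judged as changes between a post-operative and a later film. A reader who knows the nail, and who also knows which film is later, can without intent read slightly more change for Gamma3 and slightly less for InterTan.

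With a threshold as small as 3°, a fraction of a degree moves some patients across the line. The error would differ between arms and would run in the direction of the stated hypothesis. It would therefore raise the chance of a false InterTan advantage and not merely add noise.

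Neither the logistic model nor covariate adjustment can remove it afterwards. The ICC measures agreement, and two readers with the same lean agree well. The safeguard has to be in place before the films are read.

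**Working it through.** The plan gives no figure for reading error or misclassification, so there is nothing of its own to reproduce. The calculation asks only how large a lean would have to be to matter.

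**Inputs from the protocol article**
- 78 evaluable patients per arm (Sample size).
- A 3° varus threshold (Radiographic evaluation).
- A 5% test level with Holm-Bonferroni adjustment (Statistical analysis, clinical study).

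**Assumptions not in the article**
- Reader SD σ of 1.5°, 2° or 2.5° per film.
- No true varus change in either arm.
- A patient is called failed when the read change between two films is at least 3°, and for no other reason.
- A relative lean of L degrees between nails, half added to Gamma3 and half taken from InterTan, the same for every patient and both readers.
- Two-sided chi-squared test of two proportions.
- Three primary tests (radiological failure, HHS, OHS), so a Holm first step of 0.05/3 = 0.0167.

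**Step 1: proportion called failed.** The difference of two reads has SD σ√2. Hence
- Gamma3: 1 − Φ((3 − L/2)/(σ√2))
- InterTan: 1 − Φ((3 + L/2)/(σ√2))

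With σ = 2° and L = 1°, σ√2 = 2.828. Gamma3 is 1 − Φ(2.5/2.828) = 1 − Φ(0.884) = 18.8%. InterTan is 1 − Φ(3.5/2.828) = 1 − Φ(1.237) = 10.8%. That is a difference of 8.0 percentage points when nothing has moved.

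**Step 2: chance of a significant result.** The rejection probability was computed exactly by summing over both binomial distributions with 78 per arm.

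| σ | Lean | Gamma3 | InterTan | Rejects at 5% | Rejects at 0.0167 |
|---|---|---|---|---|---|
| 1.5° | 0° | 7.9% | 7.9% | 5.3% | 1.8% |
| 1.5° | 0.5° | 9.7% | 6.3% | 12.8% | 5.8% |
| 1.5° | 1° | 11.9% | 4.9% | 35.9% | 21.2% |
| 2° | 0° | 14.4% | 14.4% | 5.2% | 1.8% |
| 2° | 0.5° | 16.6% | 12.5% | 11.2% | 4.9% |
| 2° | 1° | 18.8% | 10.8% | 29.9% | 16.7% |
| 2.5° | 0° | 19.8% | 19.8% | 5.1% | 1.7% |
| 2.5° | 0.5° | 21.8% | 17.9% | 9.6% | 3.9% |
| 2.5° | 1° | 24.0% | 16.1% | 23.5% | 12.0% |

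Nearly all rejections under a lean favour InterTan. At σ = 2° and L = 1°, for example, 29.8 of the 29.9 percentage points do.

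**Step 3: sensitivity.** Adding true drift of mean 2° and SD 2° in both arms leaves the 1° result at the flat 5% level almost unchanged, at 23-39%. This variant keeps the rule that a 3° change alone is a failure, so it does not test that assumption.

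**The case against.** Several points on the other side stand and limit the claim.

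- **Visit order.** A reader might infer that the examiners will know which film is the later one. The article does not say so. It is silent on read order and film labels, and a condensed article may leave such detail to the full protocol. What can be said is that no concealment is stated.
- **Unblinding.** The sentence under Concealment mechanism describes the theatre and does not name the film examiners. It shows where the stated blinding ends, not that the examiners are deliberately unmasked. The one versus two screws give the arm away in any case.
- **From 3° to failure.** The article never says that a 3° read alone makes a device failed, or that the threshold is a difference between two films. That link is inferred. Cut-out in particular is less open to a small angular lean and would dilute the effect.
- **Test and level.** The plan adjusts by Holm-Bonferroni, so the flat 5% figures overstate the absolute rates at the first step. It also analyses device failure by logistic regression and names the chi-squared test for the complication rate. The test used above is a stand-in.
- **The lean.** Its size has no source in the article. Leans that differ between the two readers would lower inter-rater agreement, so the ICC is blind only to the shared part.
- **Existing safeguards.** Standard positioning, two examiners and digital measurement reduce random error. They do not remove a shared expectation about a visible implant.

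A reader might also take the table as evidence that a false InterTan result is likely. It is not. It shows only how sensitive the outcome would be if a lean were present.

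**Conclusion.** The point holds as a risk of bias in a primary outcome. It rests on four things the article states: the outcome is read from films, the two implants differ visibly in screw number, the hypothesis favours InterTan, and the only described blinding stops at the envelope. No protection of the examiners is stated.

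The size is illustrative. Under the assumptions above, a 0.5° lean roughly doubles the false-positive rate at a flat 5% level and takes it from about 1.8% to 4-6% at the assumed Holm step. A 1° lean gives 23-36% and 12-21% respectively. The relative inflation survives the multiplicity adjustment. The absolute figures would shrink if failure were decided mainly by components such as cut-out. The documents do not show that a lean occurs, or how large it would be. This is a cheap improvement to the reading procedure and does not show the design to be invalid.

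**What to change.** Add a paragraph to Radiographic evaluation stating that:

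- each patient's post-operative and follow-up films are exported without name, date or visit label and read in concealed random order by the two existing examiners;
- the examiners receive no clinical scores and do not read films of patients they operated on;
- angles and findings are recorded film by film, and failed or not failed is derived by program once the visit labels are restored.

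Add knowledge of the nail to the reading risks under Limitations. If the full protocol already contains such a procedure, a sentence in the article saying so is enough.

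The cost is the paragraph, the work of anonymising and shuffling files, and slightly longer reading. No extra reader or imaging is needed. Protection is partial: the nail remains visible, and healing signs such as callus will sometimes reveal the order of the films.

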#### Secondary objectives (Table 1)

**Table 1 Tab1:** Timeline chart of patient clinical evaluation

Outcome measure	Specification	Score	Assessment times				
			Pre-op	Post-op	6w	12w	24w
*Patient-reported outcome measures*							
EQ-5D-3L	General health status	5–15	√		√	√	√
SF-36	General health status	0–100	√		√	√	√
Elderly mobility scale	Fragility Assessment	0–20	√		√	√	√
SARC-F questionnaire	Sarcopenia assessment	0–10	√		√	√	√
NPRS	Joint pain	0–10	√	√	√	√	√
*Hip Joint-specific measures*							
Harris hip score (HHS)	Joint-specific score	0–100	√		√	√	√
Oxford hip score (OHS)	Joint-specific score	0–100	√		√	√	√
*Surgeon and patient related complications*			Intra-op	Post-op	√	√	√
Failure rates				Post-op	√	√	√

*NRPS* numerical pain rating scale, *SF-36* short-form 36, *EMS* elderly mobility scale, *SARC-F* strength, assistance with walking, rising from a chair, climbing stairs, and falls questionnaire, *HHS* Harris hip score, *OHS* Oxford hip score

Several secondary objectives will also be studied to evaluate the effectiveness and safety of the devices by quantifying and drawing presumptions from observed differences between treatment groups in the following:Comparison of perioperative and intraoperative surgical data (age-adjusted Carlson Comorbidity Index [41], operation time, fluoroscopy time and dosage, blood loss, length of hospital stay, prescription of pain-killers, osteoporosis assessment using postoperative DEXA of the unaffected hip, union time and intraoperative surgeon related complications, including lag screw malposition, propagation of the fracture, non-anatomical reduction, varus/valgus deformity, rotational deformity and tip-apex distance-TAD).Pain level at the perioperative period and at 6-, 12-, and 24-weeks postoperatively using the visual analogue scale (VAS) Pain Score.Patient reported general health status prior to surgery and at 6-, 12- and 24-weeks post-surgery using the SF-36 form, the EQ-5D-3L Questionnaire, the SARC-F Index and the Elderly Mobility Scale (EMS).

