#### Follow-up assessments

All the patients should undergo a clinical and radiological follow-up at 6-, 12- and 24 weeks postoperatively. The follow-up will be concluded by antero-posterior radiographs of the pelvis, lateral radiography of the treated hip and questionnaire like HHS, OHS, SF-36, EQ-5D-3L, EMS, Sarc-f, NPRS scale and Vas score.

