### Statistical analysis

The primary outcome measure of device radiological failure is considered a binary outcome (device failed/did not fail). A binary logistic regression model will be performed to assess the association between the outcome of device failure and the predictor of device type (Gamma3, Intertan). The complication rate of G3 versus InterTan at 24 weeks post-operatively would be compared using a chi-squared (at the 5% level). The differences between HHS and OHS between groups will be assessed using an independent samples *t* test at 24 weeks postoperatively at the 5% level. Test levels, will be adjusted using the methods of Holm-Bonferroni to allow for the multiple comparisons. A linear regression analysis will also be used to quantify the effects of the treatment groups on each of the primary outcome measures, after adjusting for the effects of a range of other important, potentially confounding, factors (e.g. age, gender) recorded for each patient.

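### Varus collapse is defined as an anterior rotation of at least 3°, which contradicts the protocol's own frontal-plane use of varus and may misclassify a component of the radiological primary outcome

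*Protocol article*

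**What the plan says.** The first primary aim (Primary objective) compares the two nails at 24 weeks on a list of radiological events: "cut-out, varus displacement, loss of reduction, malunion, nonunion". The clinical Statistical analysis section reduces this to one yes/no variable: "The primary outcome measure of device radiological failure is considered a binary outcome (device failed/did not fail"), modelled by logistic regression on device type.

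The Radiographic evaluation section says how the films are read. Two examiners take the measurements, with intra-class correlations for reliability. On varus it says that "throughout the follow-up the varus malalignment of the implant will be assessed", and then gives the definition at issue: "Varus collapse is a rotation of the proximal part of the femur anteriorly for at least 3" degrees.

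Positioning is fixed for one view: "For the antero-posterior ones of the pelvis, both legs of the patients will be rotated inwards 15" degrees. The Follow-up assessments section plans two views at 6, 12 and 24 weeks: "antero-posterior radiographs of the pelvis, lateral radiography of the treated hip".

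**The concern.** Varus is an angulation in the frontal plane. A rotation directed anteriorly lies in another plane. The sentence therefore names one deformity and gives the criterion for another.

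This matters because no other varus threshold is given anywhere in the article. Three terms are in use (varus displacement in the primary aim, varus malalignment and varus collapse in the film reading), and the article does not say how they relate. An examiner who has to decide whether the varus component is met has only the 3° sentence to go by. Read literally, it can pass over a hip that has collapsed in the frontal plane and flag one that has not. If one examiner reads it literally and the other gives varus its usual meaning, they are measuring different things and the reliability coefficients will mix the two.

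**Working it through.** The article gives no figure that depends on this definition. The sample size rests on the Oxford and Harris hip scores, so there is nothing to reproduce. The check is a comparison of the passages.

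**Step 1: how the article uses varus elsewhere.**

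| Place | Use |
|---|---|
| Finite element analysis | Varus or valgus reduction is studied as a departure from anatomic reduction, with native neck-shaft angle and reduction angle both set at 135° |
| Secondary objectives | Separate list entries: "non-anatomical reduction, varus/valgus deformity, rotational deformity and tip-apex distance-TAD" |
| Outcome assessment | Same separation of varus/valgus from rotational deformity |
| Limitations | Two distinct displacements: "rotational displacement is equally important to frontal plane displacement postoperatively" |
| Radiographic evaluation | Varus collapse as an anterior rotation |

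The first four agree that varus is an angular change in the frontal plane and that rotation is something else. The last conflicts with them.

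**Step 2: what a literal reading does.** Take the 135° of the finite element section as an illustrative starting angle. A loss of 3° gives 135 − 3 = 132°.

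| Hip at follow-up | Literal definition | Frontal-plane definition, same 3° |
|---|---|---|
| Neck-shaft angle 132° or less, no anterior rotation | Not collapse | Collapse |
| Neck-shaft angle still 135°, anterior rotation of 3° or more | Collapse | Not collapse |
| Both changes | Collapse | Collapse |
| Neither | Not collapse | Not collapse |

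The two readings disagree in the first two rows, in opposite directions.

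**Step 3: does it reach the primary outcome?** The primary aim names varus displacement, not varus collapse. The article never says that they are the same, so the link is an inference. It is a reasonable one, because the 3° rule is the only varus criterion offered, and the bench hypothesis (Implants; Discussion) also uses the term varus collapse.

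**Step 4: can the size be found?** With true risk p, sensitivity Se and specificity Sp, the observed risk is p × Se + (1 − p) × (1 − Sp). The article gives no failure or varus-collapse rate for this comparison, no frequency of anterior rotation without varus, and nothing on how often examiners would read the rule literally. So p, Se and Sp are all unknown, and any number would be an assumption throughout.

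**The case against.** The strongest reply is that this is a slip in one sentence. Orthopaedic examiners know what varus is, and those who apply the ordinary meaning would misclassify nothing. The same section separately assesses varus malalignment throughout follow-up, and the primary list includes loss of reduction and malunion, either of which could still catch a frontal-plane collapse. The comparison passages come from the bench work, the computer models and a list of intraoperative complications, so they show how the word is used rather than a rival clinical definition.

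Most of this stands as a limit on the consequence. It means that failures may be misclassified, not that they will be. It does not rescue the definition: a stated rule should give the right answer when followed, and this one does not.

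A reader might infer three stronger points that the document does not support.

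- *The planned imaging cannot show the event as defined.* A lateral film of the treated hip is planned alongside the antero-posterior one, and anterior angulation could be visible there. True varus can be read on the antero-posterior film. The fault is in the wording, not in the imaging.
- *The 3° cut-off lies within reader error and will dilute a true difference by a calculable amount.* The article gives no reader standard deviation. Such a calculation would also apply equally to a correctly worded neck-shaft criterion, so it does not measure the wrong-plane problem.
- *The missing reference film and the lack of a tie between cut-off and measurement error are faults in themselves.* An article may leave such detail to the full protocol.

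**Conclusion.** Wrong as written. The only numeric criterion for a varus event describes an anterior rotation and contradicts the article's own frontal-plane use of varus. Because varus displacement is a named component of the radiological primary aim, analysed as a binary failure, literal application may miss frontal-plane collapse and count a different deformity.

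The size of the effect cannot be derived from the document. The conclusion rests on one inference, that varus collapse is the working definition of varus displacement. How much it matters in practice depends on whether examiners follow the text or the usual meaning, and on how often the other listed components would catch the same hips. The sample size and the hip-score analyses are unaffected.

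**What to change.** Before any outcome film is read:

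1. Choose one term, varus displacement or varus collapse, and use it in the primary objective, the radiographic evaluation and the analysis.
2. Define it as a decrease of at least 3° in a named frontal-plane angle, for example the neck-shaft angle on the standardised antero-posterior film, from the first postoperative film to follow-up, using the mean of the two planned examiners' readings.
3. Have the sponsor confirm the stated 3° in advance. It should not be left to depend on reliability data from the trial, which would keep a primary-outcome criterion open until readings exist.
4. State that this is the varus component of radiological failure.
5. Record rotational or sagittal deformity as a separate item.

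The cost is one rewritten definition and consistent terms. The follow-up films and the two examiners stay as planned. The first postoperative film needs to be named as the baseline and taken in the same standard position.
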